## Abstract

**Background:**

The aftermath of the COVID-19 pandemic continues to affect millions worldwide, resulting in persisting postvirus complaints and impacting peoples’ quality of life. Long COVID, characterized by lingering symptoms like fatigue and mental illness, can extend beyond a few months, necessitating further research to understand its implications.

**Objective:**

This study aims to quantify the degree of physical and psychological fatigue in patients following COVID-19 infection and examine its correlation with mental health disorders.

**Methods:**

Using a consecutive nonrandom sampling technique, we will conduct a prospective cohort multicenter observational study in 5 Portuguese hospitals. Symptomatic adult patients with previous COVID-19 attending follow-up consultations will be enrolled. We will include patients who had mild, moderate, and severe acute disease. We will assess clinical outcomes related to COVID-19, including the type of respiratory support such as high-flow nasal cannula, noninvasive ventilation, and invasive mechanical ventilation. The exclusion criteria will include previous severe psychiatric disorders confirmed by a psychiatrist; refusal or inability to respond to the questionnaire; concomitant neurological disorder; persistent fatigue symptoms during the 6 months before infection; and the need for invasive mechanical ventilation during COVID-19 infection due to a high prevalence of postintensive care syndrome. Our primary outcome is the prevalence of fatigue in patients with post–COVID-19 depression and/or anxiety, as measured by the Chalder Fatigue Scale (CFQ-11) and the Hospital Anxiety and Depression Scale (HADS). The secondary outcomes will include an assessment of health-related quality of life via the EQ-5D questionnaire and an exploration of the prevalence of symptoms of posttraumatic stress disorder (PTSD) using the 14-item Posttraumatic Stress Scale (PTSS-14). We will also examine the association between mental health symptoms and the severity of acute COVID-19. The post–COVID-19 data will be collected at least 6 months after the positive test and no longer than 9 months during the clinical appointment.

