Research questions of the study.Research Question 1 (primary outcome):Do patients with long COVID who experience depression and/or anxiety symptoms have a higher prevalence of fatigue?Research questions 2 to 4 (secondary outcomes):Is there a correlation between the type of fatigue and depression and/or anxiety symptoms among patients post COVID-19?Is there a correlation between fatigue and the presence of PTSD symptoms in patients post COVID-19?Do patients with fatigue associated with mental health disorders have a lower health-related quality of life (HRQoL) after COVID-19?

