
### Power and Sample Size

We plan to conduct a prospective multicentric observational study to investigate the prevalence and severity of mental illness symptoms and fatigue in individuals with long COVID. Based on previous studies and expert opinion, we expect the prevalence of fatigue and mental symptoms in this population to be around 50% [42,43]. We aim to detect a minimum effect size of 0.2 with a power of 80% and a significance level of *P=.*05.

Using these assumptions, we performed a sample size power analysis using a 2-sample *t* test. We found that a total sample size of 200 participants (100 with adverse mental health symptoms and 100 without) would be required to detect the minimum effect size of 0.2 with 80% power and a significance level of *P=*.05. The required sample size was calculated using an a priori power analysis with an online calculator [44]. To compensate for a projected 25% loss to follow-up, we aimed for 250 participants.

We plan to recruit participants from multiple hospitals and primary care centers across Portugal, focusing on individuals who have been diagnosed with long COVID and are experiencing mental illness symptoms and/or fatigue. Recruitment will be closely monitored throughout the study to assess the pace at which participants are enrolled. The need for sample size adjustment will be determined based on the observed recruitment rates and the accumulating data. We plan to conduct an interim analysis after the recruitment of the first 100 patients.

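### The primary question compares fatigue prevalence between two groups, but the abstract words the outcome for one group and the sample size is based on a t test of means

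*Protocol article*

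**What the plan says.** The primary quantity is described in four places.

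- **Abstract, Methods:** "Our primary outcome is the prevalence of fatigue in patients with post–COVID-19 depression and/or anxiety", measured by CFQ-11 and HADS. No comparison group is named.
- **Textbox 1, Research Question 1 (marked as the primary outcome):** "Do patients with long COVID who experience depression and/or anxiety symptoms have a higher prevalence of fatigue". The word 'higher' needs a second group, and patients without those symptoms are the obvious one.
- **Methods, Primary Outcome, Fatigue:** CFQ-11 is to be used in its Likert form only (0–33). The bimodal form (0–11), which carries the case cutoff of 4 or more, is described but not adopted. Textbox 2, item 2.1, then derives fatigue cutoffs from the study's own data.
- **Methods, Power and Sample Size:** "we performed a sample size power analysis using a 2-sample *t* test". The result is "a total sample size of 200 participants (100 with adverse mental health symptoms and 100 without", said to be "required to detect the minimum effect size of 0.2 with 80% power". The same section gives a rate as its planning input: "we expect the prevalence of fatigue and mental symptoms in this population to be around 50" per cent.

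The article does not reconcile these statements.

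**The concern.** The declared question concerns a difference between two proportions. The named test concerns a difference between two means. The abstract, read literally, concerns one proportion. Each gives a different headline result: a percentage, a difference in percentages, or a difference in score points. Each also has its own precision and its own sample-size formula.

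Two things are at stake. A reader cannot tell which result is the primary one. And the justification for 200 patients cannot be checked against the primary question, because it is expressed through a test for a different kind of quantity. Since the Results section already mentions preliminary analyses, an open choice of primary quantity could come to be made after seeing data.

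**Working it through.** **Inputs from Power and Sample Size:** effect size 0.2 (scale not stated), 80% power, significance level .05 (taken as two-sided, since sidedness is not stated), 100 versus 100, expected prevalence about 50%. Normal quantiles: 1.96 and 0.8416, with (1.96 + 0.8416)² = 7.849.

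**1. The plan's figure by its stated method.** Read 0.2 as a standardised difference d, because a t test is named.

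- n per group = 2 × 7.849 / 0.2² = 392.4, so 393 per group or 786 in total. The exact t calculation gives 394 per group; a one-sided test needs 310.
- Power with 100 per group: d√(n/2) − 1.96 = 0.2 × 7.071 − 1.96 = −0.546, which is 29%.
- Detectable d at 80% power with 100 per group: 2.8016 × √(2/100) = 0.396, about 0.40.

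The 200 is not reproduced.

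**2. The same figure for Research Question 1.** Assume that 0.2 is an absolute difference in prevalence. Then n per group = [1.96√(2p̄q̄) + 0.8416√(p₁q₁ + p₂q₂)]² / 0.2², where q = 1 − p and p̄ is the mean of p₁ and p₂.

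| Prevalences | Calculation | Per group | Total | Total with continuity correction | Power at 100 per group |
|---|---|---|---|---|---|
| 40% v 60% | (1.96 × 0.7071 + 0.8416 × 0.6928)² / 0.04 = 3.877 / 0.04 | 97 | 194 | 214 | 81% |
| 50% v 70% | (1.96 × 0.6928 + 0.8416 × 0.6782)² / 0.04 = 3.720 / 0.04 | 93 | 186 | 206 | 83% |

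So 200 is consistent with a difference of about 20 points near 50%. Other readings of 0.2 also land close: a chi-square effect w = 0.2 gives 7.849 / 0.04 = 196.2, so 197 in total, and a correlation of 0.2 gives 194. Cohen's h = 0.2 does not fit (393 per group).

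**3. What 100 + 100 delivers for a prevalence comparison.**

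- Detectable difference at 80% power on the arcsine scale, with h = 0.396: starting from 50%, the other group is at 69.3%, a gap of 19.3 points. Centred on 50%, the gap is sin(0.396/2) = 0.197, or 19.7 points.
- 95% CI half-width for the difference near 50%: 1.96 × √(0.25/100 + 0.25/100) = 0.139, about 14 points.
- For comparison, a single group of 100 at 50% gives 1.96 × √(0.25/100) = 0.098, about 10 points, with no contrast to power.

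**4. Can the prevalence be computed as planned?** Not from a definition fixed in advance. The Fatigue section sets aside the only scoring for which it gives a cutoff, and Textbox 2 takes cutoffs from the same data. Aligning the abstract, the research question and the sample size would not by itself settle who counts as fatigued.

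**The case against.** The abstract is condensed and is plausibly shorthand for Research Question 1. The study objective speaks of correlation with mental health disorders, the expected results compare patients by level of depression and anxiety, and both Power and Sample Size and Results name 100 patients with and 100 without symptoms. A reader might infer that the trial will report a single percentage that cannot answer its own question. The rest of the article makes that unlikely. What stands is that the abstract's wording omits the comparator.

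A t test is also a natural choice for a 0–33 score, and the Primary Outcome section describes exactly such a score. The mean difference would be a legitimate primary estimand, and it avoids the need for a cutoff. This is a fair point, but it conflicts with the abstract and Research Question 1, both of which speak of prevalence. It shows that the mismatch extends to the outcome section and does not remove it.

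A reader might further infer that the prevalence contrast was never sized. That is too strong. The section names the right two groups, quotes a prevalence, and arrives at a total that fits a 20-point difference. A proportions calculation labelled as a t test is possible, though the article does not say so.

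Finally, a reader might infer that power for prevalence is only about 57% to 63% where a t test would have 80%. Those figures assume a true d of 0.40, normally distributed scores and, for the lower one, about 70% fatigued. The plan states none of these.

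**Conclusion.** The point holds as an inconsistency in the primary outcome and its sample-size basis. The declared question is a difference in prevalence, the stated sizing method is for means, and the outcome section retains a score without an adopted case definition. The stated method would need about 393 per group for 0.2, against the 100 given. The number 200 is nevertheless adequate for a difference of 19 to 20 points around 50%, at about 80% power.

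This rests on a two-sided 5% level, equal groups of 100 evaluable patients, and rates near the plan's 50%. The documents do not establish that the study is too small for its primary question, only that the stated justification is not one for that question. The loss-to-follow-up allowance is a separate matter.

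**What to change.** 1. **Abstract and Textbox 1:** state one primary estimand, namely the difference in fatigue prevalence between patients with and without HADS-defined depression and/or anxiety at T2, with its 95% CI.
2. **Fatigue section and Textbox 2:** fix the CFQ-11 case definition in advance so that this prevalence can be computed. The article already describes a bimodal score with a cutoff; if another definition is preferred, it should be given explicitly. Cutoffs found by optimal binning or CHAID should be labelled exploratory.
3. **Power and Sample Size:** replace the t-test basis with a two-proportion basis, giving the assumed prevalence in each group, the sidedness and the meaning of 0.2. State that 100 + 100 gives about 80% power for a 19 to 20 point difference around 50%, with a CI half-width of about 14 points.
4. **Supportive analysis:** keep the between-group difference in mean CFQ-11 Likert score, named as such.

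The cost is edits in these sections and an openly stated detectable difference. No extra patients are needed. If a case definition is added or changed after data have been seen, the date and reason should be recorded.

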**Results:**

We expect our multicenter study on patients post COVID-19 to reveal a significant link between mental illness symptoms and both physical and psychological fatigue. Patients with heightened depression and anxiety may report increased levels of fatigue. Additionally, we expect to find persistent PTSD symptoms in a subset of participants, indicating the enduring psychological impact of the virus.

**Conclusions:**

This study may underscore the need for integrated care addressing physical and mental health in patients post COVID-19. The observed connections emphasize the importance of considering mental well-being for long-term health outcomes. Despite study limitations, our findings contribute valuable insights for future treatment strategies and highlight the necessity for comprehensive mental health support in post–COVID-19 care. This research provides valuable insights into the mental health implications of COVID-19 and its impact on post–COVID-19 fatigue and the overall well-being of affected individuals.

**Trial Registration:**

ClinicalTrials.gov NCT05323318; https://clinicaltrials.gov/study/NCT05323318

**International Registered Report Identifier (IRRID):**

DERR1-10.2196/51820

## Introduction

Despite the World Health Organization (WHO) declaration marking the end of the COVID-19 pandemic on May 5, 2023 [1], millions of people continue to have postvirus complaints. Moreover, the virus remains endemic in many parts of the world. Confirmed COVID-19 cases have exceeded 430 million globally, with 200 million in Europe alone [2]. The causative agent of COVID-19 is the novel SARS-CoV-2 [3]. Although, as the name implies, respiratory symptoms are acute, the term long COVID (or post-COVID syndrome or long-haul COVID-19) began gaining recognition in the scientific and medical communities after the first descriptions of long-lasting symptoms related to mental health, such as anxiety or stress after the first infection [4]. While the definition of long COVID is unclear, the most frequent symptoms are fatigue and dyspnea [5,6]. Other less typical symptoms include cognitive and mental disorders, headache, myalgia, chest and joint pain, smell and taste dysfunction, cough, hair loss, insomnia, wheezing, rhinorrhea, sputum, and cardiac and gastrointestinal issues [4]. These symptoms may persist for up to 6 months after hospital discharge, severely impacting patients’ quality of life [7]. Since July 2021, long COVID is considered a disability under the *Americans With Disabilities* Act [8].

Per its definition, long COVID appears within 3 months after the onset of COVID-19, with symptoms lasting for at least 2 months that an alternative diagnosis [9] cannot explain, including, myalgic encephalomyelitis and chronic fatigue syndrome. However, studies have reported different persistent symptoms in contrasting durations and frequencies among survivors of long COVID [10,11]. Long COVID appears like other postviral syndromes observed in other coronavirus diseases. For example, symptoms of fatigue, myalgia, and psychiatric impairments have affected survivors of Middle East respiratory syndrome (MERS) and those with severe acute respiratory syndrome (SARS) for up to 4 years [10,12,13]. Even at 7-year and 15-year follow-ups, pulmonary and bone radiological complications were evident among a proportion of survivors of SARS who were predominantly younger than 40 years [10,14,15]. This is unsettling, as it implies that long COVID may extend beyond just a few months.

Fatigue, a primary persistent symptom of long COVID, has been reported in 10% to 70% of patients [16-19]. It is defined as “a decrease in physical or mental performance that results from changes in central, psychological, or peripheral factors due to the COVID-19 disease” [20]. Thus, post–COVID-19 fatigue depends on conditional and psychophysiological factors comprising the individual’s task, environment, physical, and mental capacity, as well as the disease’s central, psychological, and peripheral aspects [20].

While fatigue is not traditionally considered a neuropsychiatric disorder, it can be a symptom of many mental health conditions, such as depression, anxiety, and posttraumatic stress disorder (PTSD) [21,22]. Therefore, it is often included in discussions of mental health symptoms in post–COVID-19 syndrome [23]. The term “neuropsychiatric” often refers to a wide range of disorders affecting the brain and mental health. In contrast, “neuropsychological” refers to studying the relationship between brain function and behavior [24]. The primary focus of this study is on psychiatric symptoms, particularly depression and anxiety. However, we will also investigate PTSD, which is a neuropsychiatric disorder involving both neurological and psychiatric aspects. In addition, the health-related quality of life (HRQoL) assessment includes a section that evaluates aspects related to anxiety and depression. While not designed for diagnosing psychiatric disorders, this assessment can help gauge how these symptoms affect a person’s overall quality of life, making it more of a general health assessment.

The current literature on long COVID and its mental sequelae has relied on self-reported symptoms through questionnaires administered either in-person or through telephone interviews to comply with public health guidelines. However, the correlation between these self-reported symptoms needs to be clarified. There is an obvious need to accurately characterize the mental sequelae of COVID-19 and the risk factors associated with these outcomes.

This study aims to quantify the degree of physical and psychological fatigue in patients post COVID-19 and assess the correlation of fatigue with other mental sequelae—particularly depression, anxiety, and PTSD. Furthermore, we aim to explore its impact on HRQoL.

Our research questions for this study are outlined in Textbox 1.

Research questions of the study.Research Question 1 (primary outcome):Do patients with long COVID who experience depression and/or anxiety symptoms have a higher prevalence of fatigue?Research questions 2 to 4 (secondary outcomes):Is there a correlation between the type of fatigue and depression and/or anxiety symptoms among patients post COVID-19?Is there a correlation between fatigue and the presence of PTSD symptoms in patients post COVID-19?Do patients with fatigue associated with mental health disorders have a lower health-related quality of life (HRQoL) after COVID-19?

## Methods

### Overview

This protocol adheres to the SPIRIT (Standard Protocol Items: Recommendations for Interventional Trials) statement [25]. This research is designed as an observational prospective cohort study.

### Recruitment

Our study will be conducted in 1 private and 4 public Portuguese hospitals that have established follow-up post–COVID-19 medical consultations. Patients who meet the eligibility criteria will be invited to participate in the study at the end of their appointments in the follow-up clinics. This study will be conducted using a consecutive, nonrandom sampling technique.

### Inclusion Criteria

Patients who cumulatively meet the following criteria will be eligible for inclusion: (1) ≥18 years; (2) previous case of COVID-19 at least 6 months after the diagnosis that is duly documented in the clinical record; (3) persistent symptoms after COVID-19 recovery, as defined by the WHO [9]; and (4) SARS-CoV-2 RNA confirmed by a positive real-time reverse-transcription polymerase chain reaction (RT-PCR) on a nasopharyngeal swab or SARS-CoV-2 antigen confirmed with a nasopharyngeal swab by a health care professional within 7 days of initial symptoms.

We will implement multiple measures to exclude the possibility of second infections and ensure that the individuals included have persistent symptoms following their initial COVID-19 recovery. Our inclusion criteria stipulate that individuals must have a positive test result for SARS-CoV-2 RNA or antigen within 7 days after their initial infection. Additionally, we will conduct thorough reviews of medical records and clinical assessments to assess symptom presentation and timing, differentiating between persistent cases and new infections. In cases of uncertainty or potential overlap with new infections, we are prepared to conduct repeat testing, which may include RT-PCR and genomic sequencing for accurate classification.

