### Data Collection

Data collection will take place during appointments at the long COVID follow-up clinics in all participating hospitals. Qualified clinical study staff will gather the data using a clinical research form (CRF) (Multimedia Appendix 1). These individuals comprise health care professionals, such as nurses, clinical research coordinators, and health care experts who have received appropriate training and have the necessary expertise to conduct data collection and assessments in a clinical research setting. Their training ensures adherence to research protocols and ethical guidelines, guaranteeing accurate and consistent data gathering during clinical appointments. Two months after hospital discharge, we will mail all patients a letter offering a follow-up consultation in the outpatient clinic. Patients who agree to attend will be offered 2 appointments, consisting of an anamnesis and a physical examination, and given several self-administered tests in the waiting room. We will allocate 15 minutes for the questionnaire completion in the waiting room. In the first visit (T1, 3 months), the following data will be additionally collected: demographic characteristics like age, sex, and BMI (kg/m^2^); each participant’s medical history, such as the date of the first positive COVID-19 test (PCR or antigen) and smoking, alcohol, and drug consumption status; comorbidities and usual medication intake; and screening of symptoms and severity of the acute disease. Data collection in the second visit (T2, 6 months) will include post–COVID-19 symptoms, the Chalder Fatigue Scale [26] (CFQ-11), the Hospital Anxiety and Depression Scale (HADS) [27], the 14-item Posttraumatic Stress Scale (PTSS-14) adapted to COVID-19, and the EQ-5D [28] questionnaire.

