### Ethical Considerations

This study involves human participants and has adhered to all applicable ethical standards and procedures. The Algarve University Hospital Centre Ethical Committee approved this study (141/21; Multimedia Appendix 2). The patients’ race will not be included in the study because the ethics committee did not approve this differentiation. A paper-based consent form was previously approved by the ethics committee. This consent form has 2 components: information for the participant (regarding the project) and declaration of informed consent (to date and sign, in case of acceptance). The informed consent procedure, mailed to potential participants, will provide them with detailed information about the study’s objectives, risks and benefits of participation, and data management practices (Multimedia Appendix 3). The study will follow ethical guidelines and regulations related to informed consent, and participants will have the opportunity to ask questions and provide voluntary consent before enrolling. Participants will be given a month for reflection before written informed consent. As for data management, the study will implement a secure and confidential system that uses data encryption and secure storage procedures to protect participant confidentiality and comply with data protection laws and regulations. Only authorized individuals who have a legitimate need to access the data will be permitted to do so, and any data sharing will be done in compliance with the relevant ethical and legal requirements. As applicable, all procedures from this investigation followed the Declaration of Helsinki. All researchers will comply with the Data Protection Acts of their respective academic institutions.

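### Eligibility needs at least 6 months since diagnosis, but study data start at a 3-month visit, so the entry point is contradictory and the 25% loss allowance has no settled interval

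*Protocol article*

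**What the plan says.** All places are in the protocol article.

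- **Inclusion Criteria.** Four criteria apply cumulatively. The second requires a "previous case of COVID-19 at least 6 months after the diagnosis"; the third requires persistent symptoms.
- **Data Collection.** First contact is by post: "Two months after hospital discharge, we will mail all patients a letter offering a follow-up consultation". Two appointments follow. "In the first visit (T1, 3 months), the following data will be additionally collected": demographics, history, comorbidities, medication and acute severity. "Data collection in the second visit (T2, 6 months) will include" post-COVID symptoms and all four instruments (CFQ-11, HADS, PTSS-14, EQ-5D). The text does not say from which event the 3 and 6 months are counted.
- **Recruitment.** Patients who meet the eligibility criteria "will be invited to participate in the study at the end of their appointments"; whether this is T1 or T2 is not stated.
- **Ethical Considerations.** "Participants will be given a month for reflection before written informed consent".
- **Abstract, Methods.** Post-COVID data are to be collected "at least 6 months after the positive test and no longer than 9 months".
- **Power and Sample Size.** The 200 required participants are raised to 250 for a "projected 25% loss to follow-up". The Results section gives 250 as the number to be enrolled.

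**The concern.** A stated eligibility rule cannot normally be met at the stated first study visit. The statistical analysis (Textbox 2) treats the T1 items as study variables, so the visit is part of the design.

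Three things depend on where entry falls:

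1. whether the patients seen at T1 are eligible at all;
2. whether there is a period after entry in which 25% could be lost, and so how many must be enrolled;
3. whether someone symptomatic at T1 but recovered by T2 is in the analysis, since that turns on the visit at which the persistent-symptom criterion is applied.

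The primary outcome is a fatigue prevalence, so the population to which it refers has to be fixed. The description as a prospective cohort also depends on the answer.

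**Working it through.** **Step 1. Can a patient be eligible at T1?**
Eligibility needs at least 6 months since diagnosis; T1 is at 3 months.

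- *Counted from diagnosis or positive test:* 3 < 6, so criterion 2 fails for everyone at T1.
- *Counted from hospital discharge* (the only event to which the invitation letter is tied): time since diagnosis at T1 is 3 months plus the interval from diagnosis to discharge. Criterion 2 is met only if that interval is at least 6 − 3 = 3 months. That would be unusual, and it cannot apply to the nonhospitalised patients whom the Discussion says will be included, because they have no discharge date.

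**Step 2. Which visit does the text point to as entry?**

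| Reading | Text in favour | Text against |
|---|---|---|
| Entry at T1 | Letter at 2 months plus 1 month of reflection = about 3 months; a loss to follow-up needs an interval after entry | Inclusion criterion 2 |
| Entry at T2 | Only patients already meeting the criteria are invited, which means 6 months or later | All instruments are taken at T2 and no later visit is described; T1 data would precede eligibility and consent; a month of reflection does not fit an invitation at the end of the outcome visit |

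Neither reading satisfies all the sections.

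**Step 3. The loss allowance.**
Inputs: 200 evaluable and 25% loss (Power and Sample Size). Whether 200 itself follows from the stated effect size is a separate question; it is taken as given here.

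- The plan's figure: 200 × 1.25 = 250. This reproduces 250, but it is not the number that leaves 200 after a 25% loss.
- Entry at T1, 25% lost before T2: N = 200 / (1 − 0.25) = 266.7, rounded up to 267.
- What 250 delivers under 25% loss: 250 × 0.75 = 187.5, about 187.
- The loss that 250 does cover: 1 − 200/250 = 20%.
- Entry at T2: no described interval after entry, so N is about 200.

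Under either reading, 250 does not match a 25% loss to follow-up.

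**Step 4. Who is analysed?**
CFQ-11 and HADS exist only at T2.

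- If criterion 3 is applied at T1, a patient who recovers by T2 is already enrolled and contributes T2 scores.
- If it is applied at T2, the same patient is ineligible.

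The documents give no recovery rate between T1 and T2 and no fatigue or HADS levels in recovered patients, so no numerical effect on the prevalence can be computed.

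**The case against.** The best defence reads T1 as routine clinic information and entry as T2. The T1 items are mostly fixed or historical facts, so recording them at 3 months does not disturb the outcome timing, and the Abstract's 6-to-9-month window would govern the assessment. Figure 1, the enrolment flowchart, is not shown and may mark the entry point. This reading is possible, but no section states it, it leaves the loss allowance unexplained, and a flowchart could not remove the conflict between Inclusion Criteria and Data Collection.

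It can also be said that attrition may arise between first approach, the month of reflection and completing the questionnaires. If entry is at T2, loss before it is non-participation. It does not reduce the number evaluable among 250 enrolled.

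Several stronger readings are tempting and are not supported:

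- *That the primary prevalence is shifted by a known amount.* The recovery rate would have to be invented. The depression/anxiety group is defined by a scale taken only at T2, so a denominator of patients symptomatic at T1 is not a stated target. The declared population is symptomatic patients, so a prevalence conditional on persisting symptoms is legitimate if it is described as such.
- *That many T2 visits fall before the 6-month limit.* The 6 months in Data Collection can be read as a nominal label, and the Abstract gives an explicit window. No scheduling distribution is stated.
- *That diagnosis and positive test are competing time origins.* Test confirmation is itself an inclusion criterion, so they are effectively one event. The gap is that T1 and T2 have no stated origin, while the letter is dated from discharge.

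**Conclusion.** The contradiction stands in the current text. Criterion 2 cannot normally be met at T1. Moving entry to T2 makes entry and outcome assessment coincide, which leaves the 25% loss without a described interval and makes the study in effect cross-sectional for its outcomes.

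The size that can be shown concerns enrolment only: 267 are needed, or about 187 evaluable from 250, if entry is at T1; about 200 are needed if entry is at T2. These figures assume that 200 evaluable is the right requirement and that the 25% refers to enrolled patients lost before T2.

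The effect on the fatigue prevalence is real in principle, because the set of patients analysed differs, but its size cannot be derived from the documents. This is a conflict between stated rules, not detail left to a fuller document, and it should be corrected.

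**What to change.** Reconcile the Abstract's Methods, Recruitment, Inclusion Criteria, Data Collection, Ethical Considerations, and Power and Sample Size. Count T1 and T2 from the positive test, and name the visit at which criteria 2 and 3 are applied. Then follow one of two routes:

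- **Entry at T1.** Attach the 6-to-9-month condition to the outcome assessment instead of to eligibility. Restate the loss figures: 267 enrolled for 200 evaluable (17 more than planned), or keep 250 and state about 187 evaluable.
- **Entry at T2.** Drop the inflation for loss to follow-up, describe the T1 items as retrieved clinic data, and report fatigue prevalence as conditional on still being symptomatic at 6 to 9 months.

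The cost is a revision of the text, with no new measurements. The Results section gives December 2023 as the end of recruitment; if it has closed, the T1 route means stating the lower evaluable number. The downside is that the prevalence claim and the prospective-cohort description narrow slightly.
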